#### Randomisation

Clusters were allocated to the intervention or waitlist groups using a simple randomisation method of pulling community names from a hat. Participants were enrolled by a local Indigenous worker nominated by the participating service. Allocation was concealed because clusters were randomly assigned to the intervention group after enrolment of participants. There is no masking of participants, IHWs or the research team.

#### Statistical methods

The primary statistical analysis will be by intention-to-treat, using generalised linear mixed effects models, taking into account clustering by community.

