### Sample size

The trial is powered to demonstrate a reduction in mean HbA1c by 1.0% over 18 months in the intervention group compared to the control group. This estimate is based on a mean drop of 1.3% HbA1c over one year (from 9.9% to 8.6%, following initiation of intensive drug treatment in T2DM) reported by a large US Health Maintenance Organisation
[29]. A sample size of 49 in each group will have 90% power to detect a difference in mean HbA1c between the intervention and control group after 18 months of 1.0%, assuming that the common standard deviation is 1.5% using a two group t-test with a 0.050 two sided significance level. With 12 communities (six intervention, six control), this would require nine participants per community. However, due to the intervention being at the level of the health service and provider (cluster) rather than individual, the sample size needs to be inflated by the design effect, where:

$$\text{Design effect}=1+\left(\text{n}-1\right)\;\rho$$

where *n* is the average cluster number, and ρ the expected intra-class correlation coefficient for HbA1c. With n=9 and a ρ of 0.025
[22] the design effect = 1.2. Hence the required number of participants per community is 11 for the primary outcome. However, due to potential difficulty of maintaining participants in these communities in the trial, the potential for a more modest effect size in this group, and considering the relatively large number of secondary outcomes, we aim to recruit 30–35 participants in each community.

A second power calculation is based on expected reduction in avoidable hospitalisations in the intervention sites, related to the main chronic conditions. The estimated effect size is 0.08, based on the impact of the Torres Trial where an absolute reduction of 8% was achieved in the intervention sites over 12 months, and people with diabetes there were 40% less likely to be hospitalised with a diabetes-related complication compared to controls (RR=0.4)
[9]. Thus, assuming a similar effect size, a two group Chi-square test with a 0.050 two-sided significance level will have 90% power to detect a difference in absolute reduction in avoidable hospitalisations of 8%, when the sample size in each arm is 125. Again, allowing for a design effect of 1.2, this would require 150 participants in each treatment arm.

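### The stated minimum of 11 participants per community gives about 87% power, not 90%, once the 10 degrees of freedom from six communities per arm are counted; 13 are needed

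*Protocol article*

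**What the plan says.** The Sample size section of the protocol article plans for "90% power to detect a difference in mean HbA1c between the intervention and control group after 18 months of 1.0" percentage points, "assuming that the common standard deviation is 1.5" percentage points and "using a two group t-test with a 0.050 two sided significance level". From these it obtains: "A sample size of 49 in each group will have 90% power". It then spreads that number over the communities: "With 12 communities (six intervention, six control), this would require nine participants per community". The design effect is computed "With n=9 and a ρ of 0.025" and comes to 1.2, which leads to "Hence the required number of participants per community is 11 for the primary outcome".

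The section then raises the recruitment target to 30–35 per community. Its reasons are retention, the possibility of a smaller effect in this population, and the number of secondary outcomes. The small number of communities is not among them.

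The Statistical methods section says that the primary analysis is by intention to treat, "using generalised linear mixed effects models, taking into account clustering by community". It does not name the test statistic, the estimation method (ML or REML) or the degrees of freedom.

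**The concern.** Communities are the randomised units, and there are 12. The comparison between arms is a comparison of six community means with six others, so the variance of the treatment effect is estimated on 12 − 2 = 10 degrees of freedom, however many people each community contributes. A design effect inflates the variance for clustering, but the calculation still borrows the critical value and power curve of a t-test on individuals (96 degrees of freedom for 49 per group). With 10 degrees of freedom the two-sided 5% critical value is 2.228, not about 1.98, and that costs power.

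Two things are at stake. The figure of 11 is the benchmark against which losses to follow-up would naturally be judged, and it does not carry the power attached to it. In addition, if the mixed model were tested against a normal reference without a small-sample correction, the primary p-value would be too small.

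**Working it through.** **Inputs, all from the Sample size section:** difference 1.0, SD 1.5, two-sided alpha 0.05, six communities per arm, intra-class correlation (ICC) 0.025.

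**Reproducing the protocol's figure.**
- Individual t-test: noncentrality = 1.0 / (1.5 × √(2/n)). At n = 49 this is 3.30 on 96 df, power 90.4%. At n = 48 power is 89.8%. So 49 per group is correct.
- 49 / 6 = 8.2, rounded up to 9 per community.
- Design effect = 1 + (9 − 1) × 0.025 = 1.2.
- 9 × 1.2 = 10.8, rounded up to 11. The stated figure reproduces.

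**Power with the cluster-level degrees of freedom.** For m per community:
- DE = 1 + (m − 1) × 0.025
- SE = 1.5 × √(2 × DE / (6m))
- noncentrality = 1.0 / SE, referred to a noncentral t on 10 df (critical value 2.228).

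| m | DE | SE | Noncentrality | Power, 10 df | Power, 12m − 2 df |
|---|---|---|---|---|---|
| 11 | 1.25 | 0.292 | 3.43 | 86.9% | 92.5% |
| 12 | 1.275 | 0.282 | 3.54 | 89.0% | 94.0% |
| 13 | 1.30 | 0.274 | 3.65 | 90.7% | 95.2% |
| 30 | 1.725 | 0.208 | 4.82 | 99.1% | 99.8% |
| 35 | 1.85 | 0.199 | 5.02 | 99.4% | 99.9% |

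Holding the design effect at the protocol's 1.2 for m = 11 gives 88.2%, still short of 90%. The last column shows that the shortfall comes from the degrees of freedom: with individual-level df, 11 per community would exceed 90%.

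**Smaller effects at 30 per community, ICC 0.025.**

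| Difference | Power, 10 df | Power, 358 df |
|---|---|---|
| 0.75 | 90% | 95% |
| 0.6 | 74% | 82% |
| 0.5 | 58% | 67% |

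At an ICC of 0.10 (an assumption, not in the protocol), power for a difference of 1.0 at 30 per community is 82% on 10 df and 89% on 358 df.

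**Type I error if an uncorrected z test were used.** Simulation of 400,000 null trials per setting, six v six equal communities, normal outcome, critical value 1.96. ICCs other than 0.025 are assumptions.

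| Per community | ICC | REML, z | ML, z |
|---|---|---|---|
| 11 | 0.025 | 5.6% | 6.7% |
| 30 | 0.01 | 5.5% | 6.6% |
| 30 | 0.025 | 6.9% | 8.6% |
| 30 | 0.05 | 7.6% | 9.8% |
| 30 | 0.10 | 7.8% | 10.3% |

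With REML referred to t on 10 df, the error was at or below 5% in every setting run (4.1% at 30 per community and ICC 0.025). A t-test on community means held 5.0%.

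**The case against.** The strongest reply is that 11 is not the size of the trial. The same paragraph goes on to a target of 30–35 per community, where power for the stated difference is 99% even on 10 df. Since 13 suffice, a community that enrols 30 could lose 17 of them, and if all communities did so the trial would still reach 90% at the stated SD and ICC. This stands: the correction has no practical effect on power for a difference of 1.0. It does not rescue the sentence that gives 11 as the requirement. Nor does it cover the smaller effect that the section itself offers as a reason for recruiting more, where the loss is 8 to 9 percentage points at differences of 0.5 to 0.6.

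A reader might also infer that the Statistical methods section commits the trial to large-sample Wald tests with an error rate of 7–10%. The document does not support that. It names no test or reference distribution, and a REML fit with Kenward-Roger degrees of freedom would comply fully with it. Such detail is commonly left to an analysis plan, which is not shown here, so the silence is not an error. The error rates above are therefore conditional on an uncorrected z test. The roughly 10% end further needs ML and an assumed ICC of 0.05–0.10, and at 11 per community with the protocol's ICC the range is only 5.6–6.7%.

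**Conclusion.** The point holds for the sample-size statement. On the protocol's own inputs, 11 per community gives about 87% power for a difference of 1.0, about 3 percentage points below the stated 90%, and 13 are needed. The planned 30–35 is ample for that difference, so the trial is not underpowered for its stated target and recruitment need not change. Power claims for smaller effects should be read on 10 df.

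The analysis point is a safeguard, not a fault found in the text: an uncorrected z test at 30 per community would run at about 7% (REML) to 9% (ML) at ICC 0.025, and up to about 10% (ML) at assumed ICCs of 0.05–0.10.

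The power figures assume equal community sizes, the stated SD and ICC, and no covariate adjustment. The simulations also assume a normal outcome and equal communities.

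**What to change.** In the Sample size section, restate the minimum as 13 per community for 90% power, or keep 11 and give its power as 87%. Base every power statement for HbA1c on 10 degrees of freedom, including any for effects smaller than 1.0. The target of 30–35 stays.

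Before analysis, specify in the analysis plan (or confirm that it already says so) that the HbA1c mixed model is fitted by REML with Kenward-Roger or Satterthwaite degrees of freedom, or that the comparison is a t-test on community means with 10 df. These need not agree exactly if community sizes differ or individual covariates are included, so one should be named as primary. The article reports that the trial is in its intervention phase, so this can still be fixed in advance.

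The cost is a change of wording and a software option. Confidence intervals would be up to about 14% wider than with a z reference (2.228 / 1.96 = 1.137), and a 10-df reference for the REML fit can be slightly conservative when the ICC is small.

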## Discussion

Improving Indigenous health and chronic disease management have been identified nationally and in Queensland as priority areas for investment by policy makers and funding agencies
[30,31]. The rural and remote Indigenous health service delivery environment in north Queensland is characterised by high turnover of medical, nursing and allied health staff and specialist fly-in-fly-out services, hindering the systematic approach to service delivery required to effectively manage client care. Indigenous people often require additional support to access the health system, engagement with families to find effective solutions to health problems and better communication to understand the care or medications being prescribed to them
[32]. To address these issues, efforts are required to enable, train, and encourage Indigenous people to take responsibility for programs and services that affect their health and for them to work closely with existing health-care systems
[32].

This pragmatic trial will test a culturally-sound family-centred model of care with supported case management by IHWs to improve outcomes for people with complex chronic care needs. Its strong design ensures that the results will provide high quality evidence of the impact of such a model on meaningful outcomes. Other studies evaluating chronic care interventions have found that outcomes across communities can be variable
[33]. Reports of pragmatic trials need to provide sufficient details about the setting, participants and intervention for users to determine if the results are generalisable to their own situation
[34]. To this end, monitoring the fidelity of implementation to the model will be a key characteristic of the study
[35].

This trial is now in the intervention phase. We expect to report on early lessons learnt from the planning and implementation of this trial shortly.

### Ethics committee approval

This protocol received approval from the Human Research Ethics Committees of University of South Australia, Cairns and Hinterland and the University of Queensland in November 2010.

## Abbreviations

ACEI: Angiotensin Converting Enzyme inhibitor; CHD: Coronary Heart Disease; CKD: Chronic Kidney Disease; COPD: Chronic Obstructive Pulmonary Disease; CVD: Cardiovascular Disease; FTE: Full time equivalent; ICST: Indigenous Clinical Support Team; IHW: Indigenous Health Worker; NT: Northern Territory; PHC: Primary Health Care; T2DM: Type 2 Diabetes Mellitus.
